## Abstract

**Background:**

Common cold is one of the most frequently occurring illnesses in primary healthcare services and represents considerable disease burden. Common cold of Qi-deficiency syndrome (CCQDS) is an important but less addressed traditional Chinese medicine (TCM) pattern. We designed a protocol to explore the efficacy, safety, and optimal dose of Shen Guo Lao Nian Granule (SGLNG) for treating CCQDS.

**Methods/Design:**

This is a multicenter, randomized, double-blind, placebo-controlled, phase II clinical trial. A total of 240 eligible patients will be recruited from five centers. Patients are randomly assigned to high-dose group, middle-dose group, low-dose group, or control group in a 1 : 1 : 1 : 1 ratio. All drugs are required to be taken 3 times daily for 5 days with a 5-day follow-up period. Primary outcomes are duration of all symptoms, total score reduction on Jackson's scale, and TCM symptoms scale. Secondary outcomes include every single TCM symptom duration and score reduction, TCM main symptoms disappearance rate, curative effects, and comparison between Jackson's scale and TCM symptom scale.

**Ethics and Trial Registration:**

This study protocol was approved by the Ethics Committee of Clinical Trials and Biomedicine of West China Hospital of Sichuan University (number IRB-2014-12) and registered with the Chinese Clinical Trial Registry (ChiCTR-IPR-15006349).

## 1. Introduction

Common cold is one of the most frequently occurring illness present in primary healthcare services [1] and is the prototype of upper respiratory tract infection (URTI). Colds are usually caused by viral infection; rhinoviruses cause 30% to 50% of colds throughout the year and 80% of colds during peak season, and up to 200 other viruses are implicated [2]. The main symptoms are sore throat, rhinitis, rhinorrhoea, cough, and malaise [1, 3, 4]. These symptoms typically peak at 1–3 days and last 7–10 days but can persist for several weeks [3, 4]. Although common cold is self-limiting and majority of the symptoms can improve spontaneously within weeks, due to its high prevalence [3] and severe impact on a group of susceptible individuals such as children, elderly, poor sleepers [5], and patients with chronic respiratory diseases [6], it still represents a considerable societal burden associated with absence from school or work, doctor visits [7], and huge medical costs, which have been estimated to be 17 billion dollars directly and 25 billion dollars indirectly in the US per year [8].

Recent evidence has demonstrated the clinical benefits and safety of complementary and alternative medicine (CAM) for common cold [9], and traditional Chinese medicine (TCM) plays an important role in CAM. TCM is a 3000-year-old holistic system of medicine that combines medical herbs, acupuncture, food therapy, massage, and therapeutic exercise for both extensive treatment and prevention of diseases [10]. The effects of TCM on common cold have been demonstrated in a large number of clinical trials and systematic reviews in which TCM were shown to relieve symptoms and shorten the course of common cold [11–14].

Treatment based on syndrome differentiation is the character and spirit of TCM. Along with wind-cold, wind-heat, and summer-heat dampness patterns, Qi-deficiency syndrome is one of the most frequent TCM pattern in common cold [15]. Caused by insufficiency of essential Qi, manifested as fatigue, short of breath, and spontaneous perspiration, people with chronic illness, serious illness, or overworked, who can easily be attacked by exterior evil, are prone to Qi-deficiency syndrome in common cold. The invading evil may disturb the ascending and descending function of lung and spleen Qi, causing fatigue, cough, and running nose. What is worse, without sufficient essential Qi, it is difficult to dispel evil out quickly, resulting in a longer disease duration [15]. There are a number of clinical trials which assessed TCM formula for common cold with either wind-cold, wind-heat, or summer-heat dampness syndrome [16–18]; however, few studies have addressed the effects of TCM on Qi-deficiency syndrome which is an important but easily neglected syndrome pattern in common cold.

Shen Guo Lao Nian Granule (SGLNG) is based on an empirical formula of TCM for common cold of Qi-deficiency syndrome (CCQDS) and has been approved by the State Food and Drug Administration of China for a clinical trial (Certified Number: 2003L01916). It is composed of Platycarya strobilacea Sieb. et Zucc, Polygonum cuspidatum Sieb. et Zucc, Bidens pilosa L., Dendranthema indicum, E. sinica Stapf, Siraitia grosvenorii, Panax quinquefolius, Lentinus edodes, and Astragalus membranaceus Bunge (Table 1).

Unpublished pharmacodynamic studies made a rat model of CCQDS by sulphur dioxide, smoke, and cold air stimulation [19, 20]. Guided by clinical index equivalent transformation method, respiratory frequency and load swimming time of rats were carefully observed, while low respiratory rate represents short of breath in human with CCQDS, and short load swimming time means fatigue [21]. Data revealed that SGLNG can reduce cough frequency and respiratory rate and extend load swimming time. Additionally, in an in vitro study, 500 mg/mL and 1000 mg/mL of SGLNG significantly inhibited the replication of influenza virus RP8 in embryonated eggs in a simultaneous inoculation and infection model, and it also inactivated adenovirus at a concentration of 250 to 500 mg/mL. In vivo, SGLNG alleviated pathological changes of viral pneumonia in mice and had protective effects on* Haemophilus influenzae* and* Staphylococcus aureus*-induced lung inflammation. Additionally, SGLNG can reduce endotoxin-induced fever in rabbits. There was no chronic toxicity found in rats administered different doses of SGLNG (50x, 15x, and 5x normal dose) for 3 months except that blood glucose was higher in the 50x and 15x groups. Therefore, SGLNG have a significant inactivation and inhibition on respiratory tract virus infection.

A multicenter, randomized, active controlled clinical study was conducted from year 2005 to year 2007 to investigate the efficacy of SGLNG in treating common cold of Qi-deficiency syndrome (CCQDS) in patients aged between 45 and 75 years. Results showed that patients in the SGLNG group exhibited a greater reduction in symptom total score and relieving single symptoms like fatigue, muscle, and joint soreness, with no adverse event reported, compared to a classic TCM formula of Yin Qiao Jie Du Granule [22]. All of this reveals a trend for treating CCQDS by SGLNG. However, due to the disadvantages of positive-controlled trial and lacking of large samples, the exact efficacy of SGLNG in treating CCQDS and the effective dose are still unknown.

Therefore, we designed this randomized, double-blind, placebo-controlled, multicenter, phase II clinical trial to investigate the efficacy of SGLNG in treating CCQDS with the outcome measures focused on symptom reduction and to detect the optimal therapeutic dosage.

## 2. Methods/Design

### 2.1. Design

This is a multicenter, randomized, double-blind, placebo-controlled, phase II clinical study (Figure 1) adhering to the recommendations of the “CONSORT statement” [23] and the “SPIRIT statement” [24]. The study is financially supported by Hebei Baishan Pharmaceutical Co. Ltd., Hebei, China, which has played no role and will play no role in the study design, analysis, data interpretation, or decision to submit results.

#### 2.1.1. Medicinal Preparations

The main components of SGLNG are shown in Table 1. One gram of SGLNG equals 2.22 g raw plant drugs. Each component of SGLNG is produced by soaking the material in distilled water for 30 minutes, boiling it in 10 volumes of water (v/w) for 1 hour, extracting it with water twice, filtering, and condensing it to the concentration of 1 g/ml and processing it to a fine granular form by spray drying [25]. Considering the characteristics of Chinese herbal medicine, the placebo is prepared by 10-fold dilution of the study drug (SGLNG) and then condensed into granules, which are composed of 10% SGLNG and 90% maltodextrin, and the colour is made identical to SGLNG by adding artificial pigment (tartrazine, sunset yellow, and sucralose). After a 10-fold dilution, the study drug exhibits very little clinical or pharmacological effects and therefore can be used as a placebo [26]. This preparation of placebo has been used in previous studies [16]. SGLNG and placebo are nearly identical in appearance, taste, and scent and dissolve quickly in water. The production and packaging of SGLNG as well as placebo granules are provided by the sponsor unit (Hebei Baishan Pharmaceutical Co. Ltd., Hebei, China). The granules are produced in a single batch (SGLNG batch number Y140501; Placebo batch number Y140501-1). Based on the high performance liquid chromatography techniques, and good manufacturing practices (GMPs) full-range management, this company can guarantee the consistency of granule composition. All drugs are concealed in uniform packages with the same labels except drug numbers, and three bags of the test drug (the dose for one drink) are packed in a small box, with each large box containing 5 plus 1-day dosage (a total of 18 small boxes inside). Participants are isolated from each other after enrollment and are advised to take the drugs at home to avoid chatting about the drugs.

#### 2.1.2. Subjects Recruitment

We advertise the study using advertisements and posters placed on billboards in the participating hospitals and communities. Potential participants are encouraged to visit the study offices immediately when they experience cold symptoms. Participants are recruited from the out-patient departments and emergency rooms of five participating centers: West China Hospital of Sichuan University, the Affiliated Hospital of Chengdu University of TCM, the Affiliated Hospital of Changchun University of TCM, the first Affiliated Hospital of Tianjin University of TCM, and the Second Affiliated Hospital of Tianjin University of TCM. West China Hospital is the leading unit of the five centers. These centers are defined primarily geographically. All patients are required to provide their written informed consent prior to study entry.

Enrolled participants are randomly allocated to one of four groups (high-dose group, middle-dose group, low-dose group, and control group) and undergo a 5-day treatment and a 5-day follow-up (Table 3). 

#### 2.1.3. Staff Training

In each participating center, a chief investigator is appointed to be responsible for the whole clinical process (subject recruitment, intervention, follow-up, and data collection), adhering to the study protocol. All personnel involved in this trial are trained prior to trial initiation.

#### 2.1.4. Ethics and Trial Registration

Ethical approval was obtained from the Ethics Committee of Clinical Trials and Biomedicine of West China Hospital of Sichuan University (number IRB-2014-12), and the other four centers received ethical approval from local ethics committees. The study is conducted in accordance with the Declaration of Helsinki and registered with the Chinese Clinical Trial Registry (registration number: ChiCTR-IPR-15006349).

### 2.2. Objects

#### 2.2.1. Diagnostic Criteria

*Diagnostic Criteria of Western Medicine. *Participants must fulfill the following criteria [18]: (1) answering “yes” to either “do you think you have a cold?” or “do you think you are coming down with a cold?”; (2) reporting at least 1 of 4 cold symptoms: nasal discharge (runny nose), nasal obstruction (plugged or congested), sneezing, or sore (scratchy) throat; (3) scoring at least 2 points on Jackson's scale [27].

*Diagnostic Criteria of TCM. *The diagnostic criteria for common cold of Qi-deficiency syndrome (CCQDS) are based on the Guidelines for Clinical Research of New Chinese Medicine [28] (Table 2). Main symptoms include aversion to cold, stuffy, running nose with sneezing, fatigue, and shortness of breath. Secondary symptoms include fever, sore throat, headache, cough, expectoration, spontaneous perspiration, pale or red tongue, white or thin yellow tongue coat, and pulse conditions (float or weak pulse). To be diagnosed with CCQDS, patient must fulfill all symptoms listed in (1) (in Table 2) and at least one symptom listed in (2) (in Table 2) of the main symptoms, and three or more symptoms in secondary symptoms, combined with tongue and pulse conditions.

#### 2.2.2. Inclusion Criteria

Inclusion criteria are that participants are aged between 45 and 75 years; have symptoms of Qi-deficiency in normal times such as fatiguing easily, poor appetite, or suffering more frequent colds (≥6 times/year) when seasons and climates change; meet the diagnostic criteria of a common cold within 48 hours of onset; meet the diagnostic criteria of CCQDS; and possess an understanding of the trial procedure and a willingness to sign the consent form.

Although the name of the medication indicates that its possible target population might be the “elderly people,” based on the TCM pathology of common cold with Qi-deficiency, patients with younger age than the elderly patients may also present CCQDS. Therefore, in the RCT to assess the clinical efficacy of SGLNG, we extend the age of the study population from 45 to 75. This may provide broader target population for the medication and also provide evidence for phase III study in the future.

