#### 2.6.5. Primary Outcomes

*Duration of All Symptoms*. Duration of all symptoms is defined as the number of days from enrollment to the day that all symptoms disappear (the time from the symptom severity score above zero until 2 days of the severity score marked as zero). If symptom severity is marked above zero on the day after a single day of zero, the cold is defined as continuing. If the day marked above zero is the 11th day, this is defined as the end of the cold, but if symptoms last more than 11 days, follow-up will continue via phone call or e-mail until all symptoms are absent. The first day of medication administration is defined as the 1st day (day 1) in the study. The start of the day is defined as 6:00 a.m., and symptoms absent before 6:00 a.m. are regarded as occurring the day before.

Because all the participants in the trial have Qi-deficiency syndrome and normally present certain Qi-deficiency symptoms (fatigue, shortness of breath, and spontaneous perspiration), we define the disappearance of Qi-deficiency symptoms (symptom score = 0) (Table 2) as all the symptoms returning to the basic level present before the onset of common cold.

*The Total Score Reduction of Jackson's Scale*. Jackson's scale [27], which is specific for diagnosis and symptom severity assessment of common cold, contains 8 symptoms (sneezing, headache, malaise, chilliness, nasal discharge, nasal obstruction, sore throat, and cough) and rates as 0 = absent, 1 = mild, 2 = moderate, and 3 = severe. The symptom score will be summed on the 1st day and the 4th, 6th, and 11th days after intervention, and the score reduction will be calculated between the 1st day and the days after the intervention.

The symptom severity and score are assessed by researchers who are blind to the trial, and one participant is assessed by the same researcher consistently throughout trial. Participants will not be allowed to assess their overall illness or level of severity to avoid assessment bias.

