*The Total Score Reduction of TCM Symptoms Scale*. In compliance with the severity measurement of common cold in the Guidelines for Clinical Research of New Chinese Medicine [28], symptom score of CCQDS is obtained from a four-point Likert-type symptom severity scale (Table 2), with different score criteria for main symptoms and secondary symptoms: (1) main symptoms: 0 = no symptoms; 2 = mild; 4 = moderate; 6 = severe; (2) secondary symptoms: 0 = no symptoms; 1 = mild; 2 = moderate; 3 = severe. The total score of TCM symptoms (including main and secondary symptoms) will be summed on the 1st, 4th, 6th, and 11th days, and the score reduction is defined as the scores on the 1st day minus the scores after the intervention, which will be calculated on the 4th, 6th, and 11th days.

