### 2.8. Statistical Analysis

The full analysis set (FAS) is the primary analysis set for efficacy with an intention-to-treat (ITT) principle. In the FAS, all patients will be treated with at least one dose of the study drug and at least one clinical observation will be recorded in the study. All subjects without any major protocol deviations will be involved in the per-protocol set (PPS). The safety analysis will be conducted for randomized subjects who have completed at least one study visit and have safety data. Descriptive statistics will be performed on continuous variables, frequencies, and categorical variables. All symptom durations, total score reductions on Jackson's scale and TCM symptoms, the duration of each TCM symptom, the decreasing rate of TCM main symptoms, and the reduction score of TCM symptoms will be estimated with the Kaplan-Meier technique and compared using the stratified log-rank test. Comparisons among different dose groups and age layers will be conducted with an analysis of variance (ANOVA) and a least significant difference *t*-test. In this multicenter trial, the Cochran-Mantel-Haenszel test stratified by clinical centers and the logistic regression model adjusted for covariates will be used. Statistical analyses will be conducted by an independent statistician from the Health Statistics Department of the Fourth Military Medical University using the SAS statistical software 9.1.3 (SAS, Cary, North Carolina State University, North Carolina, USA).

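### Patients enter up to 48 hours after onset, but no method named for a primary outcome adjusts for hours since onset: a loss of precision, not a bias

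*Protocol article*

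**What the plan says.** All references are to the protocol article.

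- **Entry (2.2.2).** Patients must "meet the diagnostic criteria of a common cold within 48 hours of onset".
- **Natural course (1. Introduction).** "These symptoms typically peak at 1–3 days and last 7–10 days", with a tail of several weeks.
- **Duration (2.6.5).** "Duration of all symptoms is defined as the number of days from enrollment to the day that all symptoms disappear". Day 1 is the first day of medication.
- **Jackson score (2.6.5).** "the score reduction will be calculated between the 1st day and the days after the intervention".
- **TCM score (2.6.5).** "the score reduction is defined as the scores on the 1st day minus the scores after the intervention".
- **Randomization (2.4).** Stratified by center and by two age layers. Time since onset is not a stratum.
- **Analysis (2.8).** The durations and score reductions "will be estimated with the Kaplan-Meier technique and compared using the stratified log-rank test"; the strata are not named. Dose groups and age layers are compared by ANOVA and LSD t-tests. A Cochran-Mantel-Haenszel test stratified by center and a covariate-adjusted logistic model are also planned; the covariates are not listed.

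**The concern.** The entry window covers the rise of the illness and, for some patients, its peak. One patient's Day 1 score may be taken while symptoms are still building and another's when they are about to fall. The same Day 1 score can therefore be followed by quite different changes over the next three to five days, whatever the treatment. Likewise, duration counted from enrollment is the remaining part of the cold, which is up to 2 days shorter for a late entrant with the same total course.

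This variation is partly predictable from a value the sites must establish anyway to apply the 48-hour criterion. If the analysis does not use it, it stays in the error term of all three primary outcomes, in a trial with 60 patients per arm that is meant to separate three doses and a control.

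**Working it through.** **The plan's own figure.** Section 2.3 gives 50 per group at 90% power and two-sided 0.05, without an effect size or SD, so 50 cannot be reproduced. Solved backwards it implies a standardized difference d = (1.960 + 1.282) × √(2/50) = 0.648. This serves only as a scale for power below: power = Φ(0.648 / √[(2/50)(1 − R²)] − 1.960), where R² is the share of variance removed by adjustment.

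**Duration.** Assume entry uniform over 0–2 days, independent of the total length of the cold. The variance of entry time is 2²/12 = 0.333 day² (SD 0.58 day). Duration from enrollment is total duration minus entry time, so R² = 0.333 / (SD² + 0.333), where SD is that of the total cold. The document gives no SD; 2 to 3 days is an assumption. The extra patients that would give the same precision are 240 × R²/(1 − R²).

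| Assumed SD of total cold | R² | Equivalent extra patients on 240 | Power at 50 per group (90% unadjusted) |
|---|---|---|---|
| 2 days | 7.7% | 20 | 92.1% |
| 2.5 days | 5.1% | 13 | 91.4% |
| 3 days | 3.6% | 9 | 91.0% |

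**Score reductions.** The document has no data from which R² can be derived, so I used an illustrative model with 400,000 simulated courses.

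- From the Introduction: peak uniform on days 1–3, end uniform on days 7–10.
- Assumed: score at onset 40–80% of peak; linear rise and fall; independent measurement error at each visit with SD 15–35% of peak; entry uniform over 0–48 h; visits 3 and 5 days after entry (Days 4 and 6).

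Results across these inputs:

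- Mean Day 4 reduction, as a fraction of peak: −0.21 to +0.08 for entry in the first 24 h, against +0.23 to +0.33 for entry at 24–48 h.
- Share of the variance left after the Day 1 score that hours since onset explain: about 5–20% at Day 4 and 5–19% at Day 6.
- With few very early entries (triangular on 0.3–2 days, mode 1.25 days): about 2–9% on both days.
- On the power scale above, R² of 2%, 5%, 9% and 20% gives 90.6%, 91.4%, 92.5% and 95.2%.

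**Validity of the unadjusted comparison.** With no treatment effect, 50 per arm, uniform entry and total-cold SD 2.5 days, an unadjusted t-test rejected in 5.3% of 20,000 simulated trials, close to the nominal 5%.

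**Chance imbalance.** The SD of the difference in mean entry time between two arms of 60 is 0.577 × √(2/60) = 0.105 day, about 2.5 h. The two halves of the entry window differ by one day in mean entry time and by 0.25 to 0.44 of peak in Day 4 reduction. A 1-SD imbalance therefore shifts the Day 4 comparison by about 0.105 × 0.25 to 0.105 × 0.44, or 0.03 to 0.05 of peak.

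**The case against.** **Covariate lists belong in the analysis plan, which is not shown.** This stands in part. Section 2.8 names neither the log-rank strata nor the covariates, so the article neither includes nor rules out time since onset. A reader might infer that no primary outcome will be adjusted for it; the text does not support that. However, the only covariate-adjusted model named is logistic, and a fuller covariate list for that model would not help a duration or a score reduction. The point therefore concerns the methods chosen, not only an omitted list.

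**There is no bias.** This stands. A reader might infer that counting from enrollment distorts the dose comparison, or that an early/late imbalance would pass for a dose effect. Enrollment is the usual origin in a randomized trial, and randomization balances onset time in expectation. A chance imbalance is small and already covered by the type I error.

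**The gain is small and rests on assumptions.** This largely stands for duration. For the scores, entry in the first hours is doubtful: section 2.2.1 requires both group-1 main symptoms, at least one group-2 symptom and three or more secondary symptoms, while section 2.2.3 describes cold symptoms as arriving one after another. Hence the lower 2–9% range. Section 2.2.3 also gives a 5–7 day course, which the model does not use.

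**Conclusion.** The point holds as an avoidable loss of precision, not as an error of design. The text establishes the 48-hour window, a peak at 1–3 days, three primary outcomes counted from enrollment or Day 1, and no adjustment for hours since onset in any method named for them.

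The size is modest for duration: about 4–8% of variance, or 1 to 2 points of power on the trial's implied scale. It may be larger for the scores, at roughly 5–20% beyond the Day 1 score, or 2–9% if few patients enter very early. The duration figures assume uniform entry, total length independent of entry time and an SD of 2 to 3 days. The score figures depend on a model in which only the peak and end days come from the document, so they show plausibility and are not estimates for this trial. The case for acting is that the improvement is nearly free.

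**What to change.** In section 2.8, prespecify hours from symptom onset to first dose as a covariate for all three primary outcomes, with onset time recorded at Visit 1 when the 48-hour criterion is checked:

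- duration: a Cox or accelerated-failure model;
- Jackson and TCM score reductions: a linear model with the Day 1 score, center and age layer.

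If the first dose can come appreciably after randomization, count the hours to randomization so that the covariate remains a baseline value. Leave the enrollment clock and the 48-hour criterion as they are.

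The cost is a line or two of analysis text and one degree of freedom per model. Onset time is patient-reported and imprecise, which reduces the gain but introduces no bias if it is recorded before allocation. Naming the covariate in advance also avoids a disputed post hoc adjustment.
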